#### Randomization and Blinding

Participants will be allocated to intervention and control groups in a 1:1 allocation ratio. Block randomization will be conducted in random block sizes (4:4 and 2:2) to minimize selection bias. Randomization will be performed using a random number generator to assign a value to a corresponding unique study identifier, which will then be sorted in an ascending order to randomize participants to either group. A randomization list will be stored in a concealed location, password protected, and inaccessible to clinical investigators. Sequentially numbered, opaque, sealed envelopes containing the allocation will be prepared according to the randomization list by a biostatistician who is not involved in the clinical trial. The clinical investigator will administer the study treatments for every participant and will therefore be unblinded to the intervention received. Assessment and scoring of LS will be performed by a coinvestigator. Coinvestigators, data collectors, and participants will be blinded to group allocation until completion of the trial.

To minimize potential performance bias due to the clinician being unblinded, all injections follow a strict, standardized protocol regarding injection volume, anatomical injection sites, needle gauge, and injection technique. The injection process is identical for both PRP and saline groups, with a consistent approach to anesthesia, injection sites, and postprocedural care, as outlined in the study protocol (Multimedia Appendix 2).

### Ethical Considerations

This study has received ethics approval from Bellberry Human Research Ethics Committee (2017-07-546-PRE-1, PRP4LS) on October 2, 2018. All participants provided written informed consent prior to enrolment, as documented in the participant information sheet and consent form (Multimedia Appendix 1). The trial will be conducted in accordance with the National Health and Medical Research Council National Statement on Ethical Conduct in Human Research (2023) incorporating all updates [1]. Participants were informed that their participation was voluntary, that they could withdraw from the study at any time without any impact on their ongoing medical care, and that they could choose whether their data collected up to the point of withdrawal could be retained or removed from the study dataset. All data were deidentified prior to analysis. Participant identifiers were replaced with unique study codes, and no information that could directly identify participants was included in the research database. Participant details were stored in an electronic medical record system, and the deidentified study dataset was kept in a password-protected Excel file located on a secure server at the study site. Only authorized study personnel had access to identifiable data, and all records were handled in accordance with applicable privacy and data protection regulations. No monetary payment was provided to participants for their involvement in the study. Participants were required to arrange their own travel to appointments; however, travel vouchers were available upon request. Findings from this trial will be reported in accordance with the CONSORT (Consolidated Standards of Reporting Trials) statement and disseminated to the scientific community via peer-reviewed journals, conferences, medical education sessions, and patient information sessions.

### Study Intervention

#### Overview

Once enrolled, the trial will require 12 months of participants’ time across 4 appointments.

Baseline assessment + treatment 16-week assessment + treatment 26-month assessment12-month assessment

Study treatments can be administered on the same day as assessments take place. Regardless of group allocation, all participants will undergo a blood collection by a clinical nurse who will then access the randomization list and prepare either PRP or normal saline for vulval injection (Figure 1). The patient will have a physical screen to prevent them from seeing the injection to maintain participant blinding.

**Figure 1 figure1:**
[figure not shown]
Patient flow diagram. LS: lichen sclerosus; PRP: platelet-rich plasma.

#### PRP Protocol

At both treatment appointments, 8-10 mL of autologous blood will be collected from the participant into a PRP tube by using the standard phlebotomy technique (Multimedia Appendix 2). The sample is inverted several times to homogenize with the anticoagulant inside the tube. The tube is placed in a centrifuge and set to spin at 3400 rpm for 5-9 minutes. After centrifugation, approximately 4 mL of the concentrated PRP is transferred into a syringe for injection into the vulva.

#### Saline Protocol

The protocol for saline preparation is identical to the PRP protocol except that once the blood is collected into the PRP tube, it is taken out of the consultation room and discarded, and a syringe containing 4 mL of normal saline is drawn up for injection into the vulva.

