#### Injection Technique

The participant will be asked to lie in the lithotomy position on the examination table, and a topical anesthetic cream will be applied to the vulva 10-20 minutes prior to injection. The clinical nurse will hand the syringe to the clinical investigator who will inject the study preparation into the vulval mucosa in areas affected by LS by using a 30G needle. The amount injected may be less than 4 mL, if on visual inspection, it becomes evident that the tissue cannot hold the maximum amount.

The decision to administer 2 treatment sessions, spaced 6 weeks apart, was based on protocols from previous PRP studies [20,21] in dermatology and gynecology, where 2-3 sessions are commonly used to optimize tissue response and healing. The 6-week interval allows sufficient time for tissue remodeling and the biological effects of growth factors to occur between treatments. The dosage of 4 mL was selected based on the maximum safe and practical volume deliverable to the vulvar tissue, as well as the prior clinical experience in similar interventions to avoid tissue overdistension or adverse effects. The patient will be monitored for adverse effects for 15 minutes after the study treatment and will be advised not to engage in penetrative vaginal sex for 72 hours after the procedure.

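### Tube handling differs between the arms as written (PRP spun, saline tube removed and discarded without a sham spin), so participant blinding is not secured between blood draw and injection

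*Protocol article*

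**What the plan says.** All quotations are from the Methods of the Protocol article.

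- **PRP arm (PRP Protocol).** After the blood draw: "The tube is placed in a centrifuge and set to spin at 3400 rpm for 5-9 minutes". About 4 mL is then transferred to a syringe.
- **Saline arm (Saline Protocol).** Saline preparation is presented as matching the PRP procedure with one exception: "once the blood is collected into the PRP tube, it is taken out of the consultation room and discarded". Saline, 4 mL, then takes the place of PRP in the syringe.
- **Participant safeguards (Study Intervention, Overview).** In both arms, "all participants will undergo a blood collection by a clinical nurse who will then access the randomization list" and prepares the syringe. In addition: "The patient will have a physical screen to prevent them from seeing the injection to maintain participant blinding".
- **Wait before injection (Injection Technique).** In both arms, "a topical anesthetic cream will be applied to the vulva 10-20 minutes prior to injection".
- **Standardization between arms (Randomization and Blinding).** "The injection process is identical for both PRP and saline groups". The items listed there concern the injection, anesthesia and aftercare. Tube handling is not among them.
- **Blinding claim (same section).** "Coinvestigators, data collectors, and participants will be blinded to group allocation until completion of the trial".

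**The concern.** The two arms share the blood draw and the injection but not what happens in between. Taken at its word, the Saline Protocol makes removal of the tube, and the absence of a spin, specific to saline. A participant could then pick up the arm from the tube leaving the room, from a running centrifuge, or from how soon the syringe is ready.

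All the patient-reported efficacy outcomes are at stake: the pruritus and dyspareunia scales, the Dermatology Life Quality Index and the Australian Pelvic Floor Questionnaire. The Limitations section accepts that expectation may influence such outcomes, yet it states without qualification that participants are blinded. The only blinding weakness it names is the unblinded treating investigator. The first treatment precedes all three post-baseline assessments (6 weeks, 6 months, 12 months), so an arm guessed at the first visit could color every later self-report.

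**Working it through.** The plan gives no figure for this point, and the size of a bias cannot be derived from the article. The check sets the two procedures side by side and compares the stated times.

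**Step 1: the two paths**

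| Stage | PRP arm | Saline arm | Stated safeguard |
|---|---|---|---|
| Blood draw | Yes | Yes | Same in both arms |
| Tube | Centrifuged 5-9 min; location not stated | Leaves the consultation room, discarded; no spin described | None stated |
| Syringe filled | About 4 mL PRP from the tube | 4 mL saline | None stated on where this is done |
| Injection | Standardized | Standardized | Screen |

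The arms diverge only in the two middle rows. The safeguards apply to the first and last rows.

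**Step 2: can elapsed time reveal the arm?**

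Let S be the spin (5-9 min), W the anesthetic wait (10-20 min), d the minutes by which the cream precedes the blood draw, and t the extra transfer time for PRP. The added wait in the PRP arm is

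added wait = max(0, S + t - (W - d)).

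The article states neither d nor t. Taking t = 0 as an assumption:

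- Cream applied at the draw (d = 0), least favorable stated values S = 9 and W = 10: max(0, 9 - 10) = 0 min, with 1 min to spare for transfer.
- Cream applied 5 min before the draw (illustrative), S = 9, W = 10: max(0, 9 - 5) = 4 min.
- Blood drawn only once the wait is over (d = W): the added wait equals S, that is 5 to 9 min.

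Depending on an order of steps that the article does not give, the timing cue ranges from nothing to about 9 minutes, plus any transfer time.

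**Step 3: what the wait cannot mask**

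Even with an added wait of zero, two cues do not depend on time: the sight or sound of a centrifuge, and the tube being carried out in one arm only. They exist if the PRP tube is handled within the participant's sight or hearing. The wording of the Saline Protocol suggests this but does not state it.

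**Step 4: which outcomes are exposed**

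The preparation takes place at both treatment visits (baseline and 6 weeks). Patient-reported outcomes are exposed directly. The primary clinical score is rated by a blinded coinvestigator, so a participant's guess could reach it only if she disclosed it or it changed her behavior.

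**The case against.** The strongest case on the other side has five parts.

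- **The detail may lie elsewhere.** The article refers to Multimedia Appendix 2 for preparation, and that appendix is not shown. It may say where the centrifuge stands and how timing was matched. This stands: the absence of a location is not itself a fault. What remains is a difference that the article does state, with removal of the tube worded as an exception for saline.
- **The exception need not mean that PRP tubes stay in the room.** It covers a compound step: remove, discard, replace with saline. Taking the tube away may even have been meant as concealment. This stands as a possible reading, and for that reason the conclusion is conditional. If PRP tubes also left the room, the sentence is misleading and needs correcting.
- **The safeguards are better than the screen alone.** Blood is drawn in everyone, which removes the most obvious cue, and the wait can absorb the spin. Both stand, within the limits of steps 2 and 3.
- **Each participant sees only one procedure and cannot compare.** This weakens the cue but does not remove it. The information sheet is said to give intervention details, so a participant may know what PRP preparation involves.
- **The injection is called identical, the preparation is not.** This is correct. A reader might infer that the article contradicts itself, but the claim of an identical process covers the injection only, and the preparation difference is stated openly.

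A reader might also infer that the screen fails to protect blinding, or that participants were in fact unblinded. The article supports neither. The screen does what it is said to do at the injection, and nothing shows that any participant perceived the difference.

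**Conclusion.** The concern holds in conditional form. As written, tube handling differs between arms with no sham spin, and no stated safeguard covers the interval from draw to injection. Participant blinding is therefore not secured unless preparation was out of sight and hearing, or matched, in both arms.

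The difference arises at both treatment visits. The size of any resulting bias is unknown. The pruritus and dyspareunia scales, the Dermatology Life Quality Index and the Australian Pelvic Floor Questionnaire are mainly exposed, and the effect on the primary score is indirect. The conclusion assumes that Multimedia Appendix 2 does not already prescribe a matched or concealed preparation. If it does, only the sentence in the Saline Protocol needs clarifying.

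**What to change.** **For a trial using this design.** In both arms, take the tube out of the participant's sight and hearing, run the same centrifuge cycle within the anesthetic wait, and return with the syringe after the same elapsed time. In the saline arm, discard the tube after the spin. The order of cream and blood draw should be the same in both arms and stated. The cost is one extra spin per saline visit, on equipment already present: at the planned 34 saline participants and 2 visits each, 34 x 2 = 68 spins. If the spin fits within the wait, visits need not become longer.

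**For this trial.** Recruitment ended in November 2023 and the study closed in September 2024, so the procedure can no longer be changed. The results paper should report where and how tubes were handled in each arm. If the difference was perceptible to participants, it should be stated in the Limitations, and the participant-blinding claim should be qualified for the patient-reported outcomes. If PRP tubes also left the room, the Saline Protocol sentence should be corrected to say so. The cost is a few sentences.

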#### Injection Technique

The participant will be asked to lie in the lithotomy position on the examination table, and a topical anesthetic cream will be applied to the vulva 10-20 minutes prior to injection. The clinical nurse will hand the syringe to the clinical investigator who will inject the study preparation into the vulval mucosa in areas affected by LS by using a 30G needle. The amount injected may be less than 4 mL, if on visual inspection, it becomes evident that the tissue cannot hold the maximum amount.

The decision to administer 2 treatment sessions, spaced 6 weeks apart, was based on protocols from previous PRP studies [20,21] in dermatology and gynecology, where 2-3 sessions are commonly used to optimize tissue response and healing. The 6-week interval allows sufficient time for tissue remodeling and the biological effects of growth factors to occur between treatments. The dosage of 4 mL was selected based on the maximum safe and practical volume deliverable to the vulvar tissue, as well as the prior clinical experience in similar interventions to avoid tissue overdistension or adverse effects. The patient will be monitored for adverse effects for 15 minutes after the study treatment and will be advised not to engage in penetrative vaginal sex for 72 hours after the procedure.

### Data Collection

Each participant is allocated a folder containing the following documents (See Multimedia Appendix 1 and Multimedia Appendices 3-8 for example documents) (Textbox 1).

Documents in the folder of each participant.Unique study identifierSealed opaque envelope containing treatment allocationTrial information sheet and consent formAppointment scheduleBaseline demographics sheetOutcomes Assessment Package (4 copies of each):Visual Analogue Scale for pruritus and dyspareuniaClinical Scoring System for lichen sclerosusAustralian Pelvic Floor QuestionnaireDermatology Life Quality Index QuestionnaireStudy recording sheet

#### Enrollment Appointment

At enrollment, participants receive a trial information sheet outlining the purpose and aims of the trial, intervention details, duration, and participant expectations. The participant is given an opportunity to ask questions before signing a consent form. A copy of the signed consent form is scanned into their electronic medical record. A self-administered baseline demographic sheet is filled out by the participant, which has the following demographic data: name, date of birth, parity, number of children, types of delivery, menopausal status, height, weight, date diagnosed with LS, and the approximate date that the symptoms of LS were first noted (Multimedia Appendix 9).

#### Treatment Appointments

Two treatment appointments are scheduled: at baseline and 6 weeks later. After administering the treatment, the following data are recorded on the treatment record form: date, participant name and date of birth, unique study identifier, verification of venous blood collection, 2-person verification of treatment syringe contents, 2-person verification of injection of treatment syringe, and adverse reactions.

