#### Secondary Outcome Measures

Secondary outcome measures will compare changes in the subjective assessment scores over time within each group and between groups. Participants will complete the Australian Pelvic Floor Questionnaire and Dermatology Life Quality Index at each assessment appointment to evaluate changes in the subjective disease burden. The Australian Pelvic Floor Questionnaire is a validated self-administered questionnaire assessing pelvic floor symptoms, including bladder, bowel, prolapse, and sexual function symptoms, as well as symptom severity and impact on quality of life [23]. The Dermatology Life Quality Index is a validated tool assessing quality of life impairment for people experiencing inflammatory skin conditions, and a change in the score of at least 4 points is considered clinically significant [24]. A Visual Analogue Scale will be presented to participants at each assessment to record the severity of their symptoms. Participants will be asked to indicate their level of distress in relation to 2 symptoms: pruritus and dyspareunia.

The additional secondary outcomes are safety and adverse events of receiving the treatment. Autologous PRP has an advantageous safety profile due to the utilization of the patient’s own blood, which minimizes the risk of adverse events or autoimmune reactions [25]. In a pilot study undertaken by the principal investigator, all participants (n=28) reported minimal to mild pain in the 24 hours following the procedure [20]. There were no reported cases of infection, bleeding, hematoma, or other adverse effects. Adverse events will be monitored immediately after receiving the treatment, and at each assessment appointment, participants will be asked if they experienced any adverse events in the preceding period. Any adverse effects will be recorded and reported to the ethics committee.

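### Immediate adverse reactions at the two treatment visits are, as described, not observer-blinded, which does not fit the statement that data collectors are blinded or the double-blind claim for safety

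*Protocol article*

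**What the plan says.** All references are to the protocol article.

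- **Safety as an outcome.** Study Aims names safety next to efficacy. Secondary Outcome Measures states: "The additional secondary outcomes are safety and adverse events of receiving the treatment". That section gives two collection routes: monitoring straight after treatment, and a question at each assessment visit about the period since the last one.
- **The form.** Treatment Appointments says: "After administering the treatment, the following data are recorded on the treatment record form". The listed fields include a two-person check of the syringe contents and end with "2-person verification of injection of treatment syringe, and adverse reactions".
- **The staff at treatment.** Randomization and Blinding: "The clinical investigator will administer the study treatments for every participant and will therefore be unblinded to the intervention received". Under Study Intervention, Overview, every participant has a "blood collection by a clinical nurse who will then access the randomization list and prepare either PRP or normal saline".
- **The observation period.** Injection Technique: "The patient will be monitored for adverse effects for 15 minutes after the study treatment". It does not say who does the monitoring.
- **Who is blinded.** Randomization and Blinding: "Coinvestigators, data collectors, and participants will be blinded to group allocation until completion of the trial".
- **The claim made for the design.** The Background and the closing Conclusions both present the double-blind randomized design as the basis for evidence on safety as well as efficacy. Limitations calls participants and outcome assessors blinded and notes the unblinded treating investigator as a possible source of bias.

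**The concern.** Whether a mild local reaction after an injection is worth writing down is a matter of judgement. If the person deciding knows which syringe was used, that knowledge can raise or lower the recorded rate in one arm. This is detection bias, and blinding the participant removes only part of it.

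What is at stake is how far one component of a named secondary outcome may be described. A reader who takes together the statements on blinded data collectors, blinded outcome assessors and a double-blind design will conclude that every outcome, including immediate reactions, was recorded without knowledge of the arm. The account of the treatment visit does not support that for immediate reactions.

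**Working it through.** No figure in the plan bears on this point and there is nothing to recompute. The check sets the sections side by side.

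1. **When is the entry made?** After the injection, at the treatment appointment (Treatment Appointments). There are two such appointments, at baseline and at 6 weeks.
2. **What else is on the form?** Two-person checks of the syringe contents and of the injection. Whoever verifies the contents knows whether the syringe holds PRP or saline.
3. **Who is described as present?** Two roles. The injecting investigator is unblinded by explicit statement (Randomization and Blinding). The clinical nurse is unblinded by task, since that role consults the randomization list and prepares the syringe (Overview).
4. **Is a blinded observer named for the 15 minutes?** No (Injection Technique). The blinded coinvestigator's stated task is scoring LS. Assessment may fall on the same day as treatment but need not (Overview; Assessment Appointments), so that person's presence cannot be assumed.
5. **Does a stated safeguard cover the recording?** Randomization and Blinding standardizes volume, sites, needle, technique, anesthesia and postprocedural care, and gives performance bias as the reason. None of these governs who asks about, judges or records a reaction.
6. **Does the stated limitation cover it?** Only in general terms. It concerns the treating investigator and does not say that a safety outcome is recorded on the unblinded side. The same sentence calls outcome assessors blinded.

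Steps 1 to 4 lead to immediate reactions being handled by staff aware of allocation. That cannot be squared with blinded data collectors unless a further, blinded person makes the entry, and the document describes none. Steps 5 and 6 show that nothing elsewhere in the text resolves the conflict.

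**What is outside the problem.** The participant is screened from the injection and stays blinded, so symptoms the participant volunteers come from a blinded source. The question put at assessment visits is a separate route, and nothing shows that it is asked by unblinded staff.

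**The case against.** The strongest reply is that the decisive step is inferred. Treatment Appointments is written in the passive and names no recorder, the recording sheet itself is in an appendix that is not shown, and the text says data collectors are blinded. On that view this is a role left unclear in a condensed article. Part of this stands: it is not established that unblinded staff wrote the entries, nor that the form spells out the arm, since the verification could be two signatures. But the inference rests on the only two roles described at treatment, and the text then states the opposite about data collectors without an exception. That is a conflict within the document as well as a missing detail.

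A second reply is that sharing a form causes no bias in itself. This also stands. The exposure comes from who observes and judges; the shared form is evidence of who that is.

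A third reply is that the affected part is small. The pilot study cited under Secondary Outcome Measures reported minimal to mild pain over the 24 hours after the procedure. Most of that period lies beyond the 15-minute observation and can be picked up at the next assessment visit. The article also specifies no separate test of immediate reactions between arms. This is correct and limits the importance of the point.

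A reader might go further and infer that the trial's whole safety comparison is unblinded, or that the recording favors PRP. The document supports neither. The assessment-visit route is not shown to be affected, and the direction of any bias is unknown, even though the article expects a favorable safety profile for PRP.

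**Conclusion.** The point holds in a limited form. As described, the eliciting, judging and recording of immediate adverse reactions at the two treatment visits are not observer-blinded, and this conflicts with the statement on data collectors and with the unqualified double-blind claim for safety. It rests on one assumption: that the two staff roles described at treatment are the ones who complete the form. Site records naming a blinded recorder would remove it.

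No numerical size can be given. The document reports no immediate-reaction rate by arm and nothing on the extent of selective recording, so any figure would be assumption alone. The blinding of the primary outcome is not touched by this point. It is a minor matter that is cheap to correct, and it limits the wording of one part of the safety report.

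**What to change.** **For anyone reusing the protocol.** Take the adverse-reaction field off the form that carries the syringe verification. Put it on a separate sheet without arm information, completed by the blinded participant at the end of the existing 15-minute observation. Do not give this task to the coinvestigator who scores the LS clinical score: same-day attendance is optional, and being present after the injection could put the blinding of the primary outcome at risk. Cost: one extra sheet per treatment visit.

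**For this trial.** Recruitment ended in November 2023 and the study closed in September 2024 (Results), so the form can no longer be changed. In the safety report:

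- tabulate immediate reactions separately from adverse events elicited at assessment visits;
- state who recorded the immediate reactions and, unless the records show a blinded recorder, label them as recorded by staff aware of allocation;
- do not describe that comparison as double-blind.

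Cost: one label and one sentence. No clinical procedure changes.
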